### Specific aim 2: early detection of potential failure by increasing understanding of the underlying SIC mechanisms

#### Participants

A random sample of sites from each EBP that discontinue the implementation process at any point from Engagement to Competency, or that successfully achieve competency, will be recruited for participation. EBP developers estimated that eight sites across EBPs will discontinue each year. Identified sites will be asked to consent to participate in a one-time semi-structured qualitative interview using video-chat technology*.* Participants will be compensated for their time. Consenting procedures will include a request for use of the sites’ SIC data in relation to their identified data.

#### Demographics and position characteristics

Basic personal demographics (*e.g*., age, gender, education) and position characteristics (*e.g*., time in position, position level) will be assessed. Participants will be recruited from each site that was involved in the implementation effort such that programs that discontinued early on in the process might only have administrative-level participants, whereas programs that had undergone training might also have clinician-level participants.

#### Interview

Using an interview guide similar to those employed in previous studies of barriers and facilitators of EBP implementation [38,39], video-chats will be conducted by the PI and a trained qualitative research team. Interviews are anticipated to last between 1 and 1.5 hours and will utilize techniques described in detail elsewhere [40-43]. All video-chats will be digitally recorded and transcribed.

Participants will be asked a series of questions designed to elicit information on knowledge, attitudes and behavior related to the EBP, characteristics of the agency and team, the external environment, and the implementation process. For example, depending on how far they progressed in the implementation process, informants will be asked: (a) how they were involved in implementing the EBP; (b) what they know about the EBP philosophy and procedures; (c) how effective the planning process was in the pre-implementation phase (Stages 1 to 3); (d) how effective the training was in building skills in the EBP; (e) whether they believe the EBP would be helpful to the target population; (f) whether the use of EBPs changed/would change their usual pattern of service delivery; (g) whether the EBP required changes in existing agency policies or procedures; (h) what costs and benefits were encountered in using the EBP; and (i) suggested changes for the EBP to have been successfully implemented.

### Analytic plan

#### Qualitative analysis

As described by Palinkas and colleagues (2011), data from qualitative interviews will be coded for analyses [44]. Using a methodology of ‘Coding Consensus, Co-occurrence, and Comparison’ outlined by Willms [45] and rooted in grounded theory (*i.e*., theory derived from data and then illustrated by characteristic examples of data) [46], interview transcripts will be analyzed. First, investigators will prepare short descriptive ‘memos’ to document initial impressions of topics and themes and their relationships and to define the boundaries of specific codes (*i.e*., the inclusion and exclusion criteria for assigning a specific code) [47]. Then, the empirical material contained in the transcripts will be independently coded by the project investigators to condense the data into analyzable units. Segments of text ranging from a phrase to several paragraphs will be assigned codes based on *a priori* (*i.e*., from the interview guide) or emergent themes (also known as open coding) [48]. Codes will be assigned to describe connections between categories and between categories and subcategories (*i.e*., axial coding) [49]. Each text will be independently coded by at least two investigators. Disagreements in description of codes will be resolved through discussion between investigators and enhanced definition of codes. The final list of codes will consist of themes, issues, accounts of behaviors, and opinions that relate to implementation. Two investigators then will separately review transcripts to determine the level of agreement in the codes applied; agreement ranging from 66 to 97 percent depending on level of coding (general, intermediate, specific) indicates good reliability in qualitative research [50]. Based on these codes, the software QSR NVivo [51] will be used to generate a series of categories arranged in a treelike structure connecting text segments grouped into separate categories or ‘nodes’. These nodes and trees will be used to examine the association between different *a priori* and emergent categories and to identify the existence of new, previously unrecognized categories. Finally, the different categories will be further condensed into broad themes using a format that places implementation failures within the framework of the organizational and system characteristics [46]. The themes and their relationships to one another then will be organized to create a heuristic model of implementation process that can be used to develop and test hypotheses related to underlying processes of the SIC.

#### Mixed methods analysis

Data from discontinued sites’ SIC assessment, as well as their site characteristics will be examined in relation to qualitative outcomes to help increase understanding of how site behavior, as defined on the SIC, relates to on-the-ground decision-making using the mixed method technique of ‘convergence’ [44, 46, 49]. This will allow for an assessment of the SIC’s utility in providing ‘early signal detection’ of potential problems impeding successful implementation (*e.g*., does longer duration in pre-implementation most often indicate that leadership does not have an accurate understanding of how to accomplish a key implementation activity?). Thus, qualitative data will help to inform if there are reliable patterns of behaviors that are linked to particular patterns of SIC scores, thereby helping to unpack the potential for SIC scores to serve as a proxy for less easily observed phenomenon.

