**Methods/Design:**

We propose to extend the SIC to EBPs operating in child service sectors (juvenile justice, schools, substance use, child welfare). Both successful and failed implementation attempts will be scrutinized using a mixed methods design. Stage costs will be measured and examined. Both retrospective data (from previous site implementation efforts) and prospective data (from newly adopting sites) will be analyzed. The influence of pre-implementation on implementation and sustainability outcomes will be examined (Aim 1). Mixed methods procedures will focus on increasing understanding of the process of implementation failure in an effort to determine if the SIC can provide early detection of sites that are unlikely to succeed (Aim 2). Study activities will include cost mapping of SIC stages and an examination of the relationship between implementation costs and implementation performance (Aim 3).

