#### Learning from failures and success

Although organizational factors such as climate and culture have repeatedly demonstrated influence on successful implementation [16], less is known about when failures occur in the implementation process and what the site’s perceptions are as to why these failures occurred. Much can be learned from sites that initiate the implementation of an EBP and then fail to reach milestones such as start-up or sustainability [17] in addition to those that are successful. Until recently, studies recruited sites retrospectively [11] or used recruitment designs where EBP champions recruited sites to implement [7], therefore not reflecting real-world conditions in which sites often initiate the process. We propose a naturally occurring design in which sites self-select to adopt a practice. This allows for prospective observation of the specific barriers that are perceived by sites as insurmountable at particular stages in the implementation process, and the differences between sites that are and are not able to overcome them. We will evaluate if barriers that result in failure can be detected using a standardized measure.

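### Aim 2 interviews both discontinued and successful sites, but its mixed methods analysis links the interviews to SIC data from discontinued sites alone

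*Protocol article*

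**What the plan says.** The abstract (Methods/Design) commits to both kinds of site: "Both successful and failed implementation attempts will be scrutinized using a mixed methods design". The Background section on learning from failures and success says the design allows observation of perceived barriers and "the differences between sites that are and are not able to overcome them".

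Under Specific aim 2, Participants, a random sample is drawn of sites that discontinue at any stage "or that successfully achieve competency, will be recruited for participation". On linkage the same section says: "Consenting procedures will include a request for use of the sites’ SIC data in relation to their identified data". It gives one number: "EBP developers estimated that eight sites across EBPs will discontinue each year". No number is given for successful sites.

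The Mixed methods analysis section is the only place that specifies how interview findings are joined to SIC scores. It reads "Data from discontinued sites’ SIC assessment, as well as their site characteristics will be examined in relation to qualitative outcomes", and then: "This will allow for an assessment of the SIC’s utility in providing ‘early signal detection’ of potential problems impeding successful implementation". Its example asks whether a long pre-implementation duration usually reflects leadership's misunderstanding of how to carry out a key activity.

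**The concern.** A SIC pattern and the explanation behind it are useful as an early signal only if they are less common in sites that go on to succeed. The stated linkage looks at sites chosen because they failed and gives successful sites' SIC data no role, although those sites are interviewed and asked for consent to its use. A barrier that most sites meet and many overcome would look the same in this analysis as a barrier that stops sites.

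What is at stake is the interpretive half of Aim 2: whether the reasons found behind a SIC score are particular to failing sites or shared by all sites with that score.

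**Working it through.** **Passages side by side**

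| Step | Sites covered | Where |
|---|---|---|
| Scope of mixed methods | Successful and failed | Abstract, Methods/Design |
| Recruitment and interview | Discontinued and competency-achieving | Specific aim 2, Participants |
| Consent to use SIC data | Requested of identified sites, with no limit by outcome | Specific aim 2, Participants |
| Coding of transcripts | Not limited by outcome, though final themes are framed around failures | Qualitative analysis |
| Linkage of interviews to SIC scores | Discontinued sites named, no other group | Mixed methods analysis |
| SIC scores against milestones (Cox models) | Not limited to discontinued sites, no interview data | Implementation performance: hypothesis testing |

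The linkage row is narrower than every row above it. The Cox row has the comparison but lacks the interviews. No row has both.

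**What discontinued sites alone leave unknown**

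The article states no figure to reproduce, so this uses assumed values to show the mechanism. Take the section's own example. Among sites with a long pre-implementation duration, let

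- p = share that discontinue, assumed 0.50;
- a = share of slow discontinued sites showing the theme, assumed 0.80;
- b = share of slow successful sites showing the theme, which discontinued sites cannot tell us.

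Share of all slow sites with the theme = p·a + (1 − p)·b. 
Share that fail among slow sites with the theme = p·a / [p·a + (1 − p)·b].

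| b | Theme among all slow sites | Failure among slow sites with the theme | Reported from discontinued sites |
|---|---|---|---|
| 0 | 0.40 + 0 = 0.40 | 0.40/0.40 = 1.00 | 0.80 |
| 0.20 | 0.40 + 0.10 = 0.50 | 0.40/0.50 = 0.80 | 0.80 |
| 0.80 | 0.40 + 0.40 = 0.80 | 0.40/0.80 = 0.50 | 0.80 |
| 1 | 0.40 + 0.50 = 0.90 | 0.40/0.90 = 0.44 | 0.80 |

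At b = 0.80 the theme adds nothing to the assumed 50% failure rate of slow sites. At b = 0.20 it raises that rate to 80%. The last column is the same in every row. Other values of p and a change the figures but not the conclusion, because b cannot be estimated from discontinued sites.

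The second column matters for the section's own example. When a score is read as a signal, the site's outcome is not yet known, so asking what a long duration usually indicates is a question about all slow sites. Restricting to failures answers it correctly only if b equals a.

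**Numbers available**

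Eight discontinuations a year over three participating EBPs is 8/3, or about 2.7 per EBP per year, before sampling and consent. Any comparison will be descriptive.

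**The case against.** The strongest reply is that the comparison of failure with success belongs to Aim 1. There, sites are clustered on Proportion and Duration and Cox models are fitted to milestones such as start-up and certification, with no restriction to failed sites. This stands. A reader might infer from the Mixed methods analysis section that the plan never tests whether SIC scores separate failing from succeeding sites, or that long durations common to all sites would be reported as warning signs. The article does not support that: Aim 1 tests whether duration discriminates. What Aim 1 cannot test is whether the explanation behind a duration discriminates.

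A second reply is that this section interprets scores and does not predict failure. The Aim 2 heading speaks of understanding mechanisms, and the section closes on scores as a proxy for things harder to observe. This stands in part, and it is why one cannot say that Aim 2 goes unanswered. But the abstract words Aim 2 as determining whether the SIC can detect early the sites unlikely to succeed, and the interpretive question is itself distorted by conditioning on failure.

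A third reply is that the section never excludes successful sites, that their transcripts are coded, and that the Discussion (Prediction) mentions relating SIC data to end-user interviews without restriction. It is true that the restriction follows from naming one group, and loose drafting is a likely cause. Still, no section states the linked comparison, and an analyst following the text would not make it.

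Finally, diagnostic-accuracy statistics suit a small qualitative sample poorly, and masking coders to outcome is largely impractical because interview questions depend on how far the site progressed. Both points are accepted.

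**Conclusion.** The point holds in a limited form. The article's recruitment, consent and stated scope cover both groups, while the one analysis that joins interviews to SIC scores names discontinued sites alone. Followed as written, it cannot show whether the reasons behind a SIC pattern are specific to failing sites or shared by successful ones.

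The size cannot be fixed from the article, which gives neither a discontinuation rate nor any theme frequency. The range of 40% to 90% in the working rests wholly on assumed values and shows only how much is left undetermined. The conclusion itself rests on two readings: that the sentence means the group it names, and that no other section supplies the linked comparison. It does not extend to Aim 1, nor to a claim that Aim 2 fails as a whole.

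**What to change.** Reword the Mixed methods analysis section so that SIC data and site characteristics from all interviewed sites, discontinued and successful, are examined against the qualitative findings. Add that, for each SIC pattern linked to a theme, its frequency will be described separately in the two groups and compared at the same SIC stages, so that a site that stopped early is set against the early stages of sites that went on. Because sites are sampled by outcome, the two frequencies should be reported side by side and not pooled into one rate.

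Formal sensitivity and specificity estimates and masking of coders are not needed.

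The cost is modest extra analysis on sites already to be recruited and interviewed. It is not nil: the number of successful sites to be interviewed is not stated, linkage depends on consent, and with about eight discontinuations a year across EBPs the comparisons will be imprecise. The Trial status section puts the study about one year in, with tools for the main prospective period still being developed, so the change can be made in time.

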## Specific aim 3: costs by stage and implementation outcomes

### Cost mapping utilizing the SIC

#### Data collection

At the initial adaptation meeting, an assessment of the developers/purveyors’ perceptions of effort, resources and fees associated with each of the identified activities was conducted. Throughout prospective data collection procedures, data will be collected regarding the estimated person hours and resources used by sites to complete the SIC activities.

#### Additional costing procedures

Although resources such as person hours and fixed fees will be identified through the data collection calls, additional efforts will be necessary to cost implementation activities. Wherever possible, cost components such as wages and travel costs will be based on national average estimates in order to maximize the generalizability of the results and minimize the potential that performance sites are not typical with respect to salary structures. National public databases, such as the Bureau of Labor Statistics, will be accessed to determine cost estimates for variables such as travel expenses, salaries, and meeting expenses for activities related to implementation.

### Analytic plan

#### Cost estimates

There are three varieties of costs to measure within each stage of the SIC to evaluate the cost of implementation. First, there are direct costs of the implementation services to the site, which generally consist of fees charged by the EBP purveyor. Second, there are indirect costs of site personnel time that is spent conducting the implementation (*i.e*., doing things that do not directly produce client services, and which will not be necessary once implementation is complete). Third, there are ancillary costs, which are made up of the actual infrastructure investments that are required for implementation (*e.g*., the costs of installing a new IT system for fidelity monitoring).

Direct costs will be measured as invoices from the EBP vendor to the site for services and support provided in each stage of the SIC. Indirect and ancillary costs will be measured using a time/resource log designed as part of the project. Each EBP will require a slightly different tool that will depend on the specific nature of the intervention, and will assess personnel (*e.g*., therapists, administration) and other costs that pertain to the implementation but not to the provision of clinical services to clients. We will collect unit cost (such as personnel time), and to the extent possible, use national data to generate the cost weights so that the estimated indirect costs will be representative of what a randomly selected program could expect.

Costs of implementation will be expressed as average cost per SIC stage for each site. However, the raw average cost will not describe the range of possibilities. For example, a site that takes longer to move through an SIC stage will probably have a higher cost for that stage, and merely including it in an average cost calculation would be misleading. Consequently, regression techniques will be used to estimate risk-adjusted cost functions, which can vary with such factors as the number of clients treated by a program or the time required to move through each stage of the SIC. The dependent variable of the regression will be the logged implementation cost for each stage for each site. Ranges of costs will be imputed using the regression models, where staged implementation costs, and 95% confidence intervals for those costs, will be imputed by applying the Duan smearing estimate to predict the levels of SIC stage costs from the logged cost regression.

#### Implementation performance and cost

Using regression models for each EBP, variations in cost will be examined as they relate to SIC scores. Assumedly, longer Duration scores will increase resource allocation needs, but perhaps not significantly. The costs that are mapped onto activities will be calculated in relation to individual activities as well as stages. Cost curves will be estimated to help inform the optimal rate and Proportion of activity completion for sites to achieve success. It might be the case that sites that have higher initial costs (*e.g*., due to a high Duration) are more likely to have low Proportion scores during later stages (*i.e*., attempting to reduce implementation costs downstream). These variations will be considered in relation to successful achievement of implementation milestones.

### Trial status

This protocol has been underway for approximately one year. The study protocol has been approved by the Institutional Review Board. All site visits and initial adaptations have taken place, with each adaptation having gone through several revisions. MST and MDFT are nearing completion of their retrospective data collection, whereas the CC program is well into prospective data collection. Data collection tools for the next study period focused on prospective data collection across all sites are under development, including the cost and resource logs specific for each practice. Current efforts are underway to identify universal items across each of the three adaptations compared to the original MTFC-SIC.

## Discussion

During the final year of study procedures for each EBP, developers will be collaboratively involved in determining the most beneficial uses of the SIC. All EBP-specific outcomes will be shared, and the way that the SIC operates for each EBP will be explained to the developers. For example, the original MTFC-SIC outcomes indicated that sites that linger too long in the pre-implementation phase are less likely to achieve successful program start-up; the EBP developers/researchers might use this information to inform future modifications to their implementation process such as developing an enhanced protocol for struggling sites. Similarly, the developers/purveyors might determine that such information is important feedback for sites as they decide if it is in their best interest to proceed or not. In order for the EBPs to benefit from the SIC, a full understanding of the scoring methods, interpretation, and potential utility must be conveyed.

### Innovation

We believe that the proposed work is innovative in three primary ways.

### Generalization

Adopters, EBP developers, and researchers could all benefit from having a measure that helps determine early on and throughout the implementation process if sites are doing well, doing poorly, or just ‘getting by.’ For adopters, such information would allow for ongoing progress monitoring and could inform decisions about potential corrections. For developers, being able to see where sites are struggling would allow for the development of strategic methods for improving their support. For researchers, such measures of process are needed to begin testing the efficacy of existing implementation approaches and frameworks.

### Prediction

The expansion of the SIC will allow for the evaluation of site implementation behavior through observation of progress (both time to completion of key tasks and proportion of tasks completed), thereby providing fine-grained data on progress toward the attainment of key implementation objectives. Such data can serve as ‘milestone implementation outcomes’ in and of themselves. In the proposed study, achievement of these outcomes will be observed within and across the practices being studied. At each stage, data on time to completion and proportion of tasks completed during previous stages can be used to predict future milestone achievement at later stages. This data will be considered in relation to qualitative data collected from end-users to increase understanding of the underlying mechanisms assessed by SIC scores. This type of fine-grained data will allow for an examination of which implementation activities are crucial for program success and which might be encouraged but are not essential.

